### 2.3. Inclusion and Exclusion Criteria

#### 2.3.1. Inclusion Criteria

The inclusion criteria are as follows:
(1)Age 18–65 years;(2)Diagnosis of schizophrenia by ICD-10 (F20);(3)PANSS negative subscale, minimum ≥4 on two of the following items, blurred affect (N1), emotional withdrawal (N2), poor contact (N3), passive apathetic social withdrawal (N4) and lack of spontaneity and flow in dialogues (N6).

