### 2.7. Sample Size

#### Estimation of Sample Size

Utilizing previous data, we estimated an effect size of 0.6 (medium effect according to Cohen’s d). With a selected level of significance of 0.05 and a power of 0.8, a power calculation performed in R with a conservative approach (applying a two-sided *t*-test with two samples), resulted in each group having to count a minimum of 44.5 persons. The data utilized in the power calculation did not use an active comparator, which might result in a lower effect size in the current study. We furthermore estimate a drop-out of 10–20% of participants, resulting in an estimated required sample size of 60 persons in each group.

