## 3. Results

### 3.1. Statistical Analysis

#### 3.1.1. Form of Statistical Analysis

As the study is still running, no final results are available. The results will be generated through statistical analysis where the endpoints from PANSS, BNSS and WHOQOL-BREF will be analyzed using mixed model effect analysis. Predictors for the response to the treatment will be performed by multiple logistic regression, using the severity of psychiatric disorders, timespan from diagnosis identified, psychotropic medication, PANSS score results and regional contra communal treatment as usual, as explanatory variables with a regression model being performed for each of the two randomized groups. The analysis will focus on identifying predictors of improvement of negative symptoms and change of quality of life, alliance and global functioning, as well as predictors for improvement connected to treatment (music therapy activities I or II). Both per protocol and intention-to-treat analyses will be performed. Intention to treat is defined as utilizing data from all participants, even if the single participant has not attended all 25 sessions. At the time of discontinuation from the study, a final assessment will be conducted, if possible. Participants will not be followed up on after this time point.

All tests will be applied double sided and the significance limit is defined as *p* < 0.05.

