## Figures and Tables

**Figure 1 medicines-06-00046-f001:**
[figure not shown]
Flow diagram of the experiment design. As the recruitment process is currently running, only the inclusion data can be presented.

**Table 1 medicines-06-00046-t001:** A SPIRIT diagram on screening procedures.

	Screening	Baseline		After Fifth before Sixth Offered Session	After Fifteenth before Sixteenth Offered Session			Less Than Eight Days after the Last Session Termination ^1^			Follow up 4–5 Weeks after Termination
No of visit	1	2		3	4			5			6
Performed by ^2^			MT/T	RP	PN	MT	RP	PN	MT	RP	RP
Information and consent	x										
Demographical data ^3^	x										x
Status of medicine	x	x ^4^			x			x			
History of abuse	x	x ^4^			x			x			
History of music therapy ^5^	x	x ^4^									
Inclusion and Randomization		X									
PANSS	x	x ^6^			x			x			
Brief Negative Symptom Scale (BNSS)	x	x ^4^			x			x			
WHOQOL	x	x ^4^			x			x			
Calgary Depression Scale for Schizophrenia (CDSS)	x	x ^4^			x			x			
Udvalg for Kliniske Undersøgelser (UKU), otherwise Task Force for Clinical Investigations	x	x ^4^			x			x			
Global Assessment of Functioning (GAF)	x	x ^4^									
Helping Alliance Questionnaire (HAQ-II)				x			x			x	
MIRS Only experimental group I			x			x			x		
Start of weekly interventions, groups I and II			x								
Start McGlashan rating after each intervention for experimental group I			x								
Termination of weekly interventions for groups I and II									x		
Interview											x

^1^ Is not performed if screening procedure after fifteenth session but before sixteenth offered session is performed ≤14 days earlier. ^2^ PN = rroject nurses; MT = music therapists group I, therapist group II; RP = research participant. ^3^ Sex, age, ethnicity, level of education, social and work situation. ^4^ Is not performed if performed by screening ≤28 days earlier. ^5^ Music therapy and other formalized music related offers other than trial treatment are registered. ^6^ Is not performed if positive and negative syndrome scale (PANSS) in screening is performed ≤14 days earlier.

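### PANSS scores are listed as predictors of negative-symptom improvement in separate per-arm models, which cannot tell a real severity effect from regression to the mean

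*Protocol article*

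**What the plan says.** Section 3.1.1 of the protocol article describes a multiple logistic regression for response to treatment. Among the covariates are "PANSS score results and regional contra communal treatment as usual, as explanatory variables". One model is fitted in each randomised group. The stated aim includes "identifying predictors of improvement of negative symptoms and change of quality of life", together with alliance, global functioning and predictors linked to which of the two activities was received.

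Three other places bear on this:

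- Section 2.4 makes change in the PANSS negative subscale the primary outcome.
- Section 2.3.1 selects participants on items of that subscale: "PANSS negative subscale, minimum ≥4 on two of the following items".
- Table 1, footnote 6, says of the baseline PANSS: "Is not performed if positive and negative syndrome scale (PANSS) in screening is performed ≤14 days earlier". Section 2.2 requires the first session within 14 days of screening, so reuse of the screening rating as baseline is the expected course.

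The article does not say which PANSS score or visit the predictor comes from, nor how improvement becomes a yes/no response.

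**The concern.** On the natural reading, the baseline PANSS negative score is both the predictor and the first term of the change it is meant to predict. Measurement error and passing fluctuation in that score then enter both sides. Someone rated too high at baseline will on average be rated lower later, and this counts as improvement even if true severity has no bearing on response. Within one arm there is nothing to set this against, so the baseline coefficient mixes the artefact with any real effect.

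The Abstract and section 1.1.2 place the trial in the context of guideline recommendations. A reported finding that severity predicts response could be used to decide who is offered the treatment.

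**Working it through.** **The plan's own figure.** No figure is given for the predictor analysis. The only sample-size calculation is in section 2.7: a two-sample t-test, two-sided at 5%, with 80% power for a standardised difference of 0.6. It gives 44.5 per group. A noncentral-t calculation gives 44.59, so it reproduces; it is not in dispute here. For arm size I use 30 (the current aim of 60 in total, section 5) and 45 (the 90 in total in the Abstract).

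**Coupling with equal variances.** Let B be the baseline score and E the end score, with common SD σ and correlation ρ.

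- Cov(B, B−E) = σ²(1−ρ) and Var(B−E) = 2σ²(1−ρ).
- So corr(B, B−E) = √((1−ρ)/2).
- ρ = 0.5: √0.25 = 0.50. ρ = 0.7: √0.15 = 0.39. ρ = 0.9: √0.05 = 0.22.

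**Coupling with true change independent of true severity.** Let R be the reliability and s the SD of true change in baseline SDs.

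- corr(B, B−E) = (1−R)/√(s² + 2(1−R)).
- With s = 0.5 (assumed), R = 0.8: 0.2/√0.65 = 0.25. R = 0.6: 0.4/√1.05 = 0.39.
- These values apply before any selection on B.

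**Chance of a false finding in at least one arm.** Simulation under that second model: 27-30 per arm, response = above-median absolute improvement, one logistic model per arm, Wald test at 0.05. Two valid independent tests would give 1 − 0.95² = 9.75%.

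| Reliability (assumed) | No selection | Upper half selected on the same rating |
|---|---|---|
| 0.8 | 28-30% | 13-14% |
| 0.7 | 42-45% | 17-21% |
| 0.6 | 53-60% | 24-27% |

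The right-hand column is the closer match, because section 2.3.1 selects on this scale. Selection narrows the baseline range and so lowers the rate. With selection and reliability of about 0.85-0.90, the rate is about 8-12%, essentially nominal.

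**Dependence on the response rule.** One arm, no treatment effect, equal mean and SD before and after (24 and 5, assumed), no selection. Each cell gives the approximate odds ratio per SD of baseline and the share significant at n = 30 / n = 45.

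| Assumed response rule | ρ = 0.5 | ρ = 0.7 | ρ = 0.9 |
|---|---|---|---|
| Drop of at least 3 points | 2.6-2.8; 47% / 71% | 2.2; 28% / 47% | 1.6; 6% / 12% |
| At least 20% reduction above the scale minimum | 1.8-2.0; 19% / 31% | 1.3; 4% / 8% | 0.6; 5% / 10% |
| End score of 20 or less | 0.32-0.37; 48% / 69% | 0.15-0.17; 78% / 95% | 0.02; 69% / 94% |

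The same null data can make severe patients look like better responders, no different, or worse responders.

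**Comparing the slope between arms.** With the 3-point rule and the same null, the difference in baseline slopes between arms is significant in 3.2-4.0% of runs (n = 30 or 45 per arm, ρ 0.5-0.9). A linear baseline-by-arm interaction under the reliability model gives 4.2-5.7%. The artefact is equal in both arms and cancels. This was checked with no treatment effect present.

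**The case against.** The strongest reply is that the article leaves the decisive details open. The score could be the PANSS positive or general subscale, improvement could be read on the BNSS, and a full protocol or analysis plan may settle both. The same covariate list also serves quality of life, alliance and global functioning, where no score need appear on both sides. This stands to the extent that the point is conditional, and the missing definitions are not themselves the fault. It does not remove the point: change on the PANSS negative subscale is the primary outcome, the PANSS total contains the seven negative items, and the per-arm structure is stated. With the BNSS as outcome the artefact should be weaker, but fluctuation can still be shared, since both scales are scheduled at the same visits.

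A second reply is that reliability may be high. Section 2.4.1 cites 0.83-0.90 with the structured interview, and in that range, with selection, the false-positive rate is about nominal. This partly stands. Those coefficients describe agreement between raters, not a patient's fluctuation over 25 or more weeks, so lower values are plausible, but they remain an assumption.

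A reader might also infer three stronger things that the documents do not support:

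- That regression to the mean by itself is bound to make severe patients look like better responders. The second table shows that the direction follows a response rule the article does not give.
- That selecting on the same rating makes the problem worse. For the within-arm slope it reduces the false-positive rate.
- That the trial's main result is biased. The randomised comparison uses a mixed model, and both arms regress alike.

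**Conclusion.** The point holds in conditional form. If the predictor is the baseline PANSS negative subscale or the PANSS total, and improvement is read on the negative subscale, the planned per-arm models cannot distinguish a severity effect from regression to the mean and coupling. The excess of false findings is moderate: about 13-27% against about 10% for two valid tests, and none to speak of at reliability of 0.85-0.9. These figures assume reliability of 0.6-0.8, above-median absolute improvement, upper-half selection on the same rating and about 30 per arm; none of the first three is given in the article. The consequence is confined to the secondary predictor analysis. It still merits a change, because a coefficient whose sign turns on the response definition should not be read as a clinical predictor.

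**What to change.** In section 3.1.1, for the outcome of negative-symptom improvement:

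- Fit one pooled model with arm, and enter baseline PANSS negative as an adjustment term whose main effect is not interpreted as a predictor. Do not interpret the PANSS total either, since it contains the negative items.
- Assess severity as an effect modifier only through the interaction of baseline PANSS negative with arm. This also answers the section's own aim of finding predictors tied to which activity was received, which two separate models do not test.
- The PANSS positive and general psychopathology subscales may stay as candidate predictors.

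This is a change of wording only, as the scores are already collected. It costs one reported predictor. The interaction will also have low power at about 30 per arm: a difference between two independent slopes has a standard error √2 ≈ 1.41 times that of one slope when the two are equally precise. A null interaction should therefore not be reported as evidence that severity does not matter.

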## 5. Conclusions

### Reduction in Sample Size Due to Challenges

The trial status is currently ongoing. Recruitment started in March 2016 and will continue until the end of May 2019, with the expected last participant visit in December 2019. Due to low rates of recruitment, a total of 47 participants have been included by November 2018, from the 177 referred to the study (see Figure 1). We currently aim to include a total of 60 participants. Concerning blinding, we have currently been informed that three participants receiving intervention II have expressed that they know they are not receiving music therapy due to previous experiences with music therapy. So they are not blinded. This will be transparent in the analysis of the data. In spite of challenges concerning motivation and attendance, many participants have so far been able to attend all sessions offered. The results of the current trial will be widely disseminated at national and international scientific conferences and in further scientific articles.

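### The predictor analysis fits a separate five-variable logistic model in each arm, so as planned it does not test whether a predictor's effect differs by treatment, and at 24–30 per arm the models are badly overfitted

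*Protocol article*

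**What the plan says.** All of the relevant method is in section 3.1.1 of the protocol article:

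- Model: "Predictors for the response to the treatment will be performed by multiple logistic regression".
- Explanatory variables, five in number: "using the severity of psychiatric disorders, timespan from diagnosis identified, psychotropic medication, PANSS score results and regional contra communal treatment as usual".
- Structure: "with a regression model being performed for each of the two randomized groups".
- Aim: predictors of improvement in negative symptoms and of change in quality of life, alliance and global functioning, "as well as predictors for improvement connected to treatment (music therapy activities I or II".

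The section sets two-sided testing at p < 0.05. It gives no definition of a responder, no treatment-by-predictor term and no comparison of the two sets of coefficients.

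On size, section 5 says: "We currently aim to include a total of 60 participants". It also reports that "a total of 47 participants have been included by November 2018". Section 2.7 adds: "We furthermore estimate a drop-out of 10–20% of participants".

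**The concern.** The method does not match the aim. To say that a predictor is connected to one activity rather than the other, its effect must be compared between arms. Two models fitted apart each describe their own arm, and neither contains that contrast. With no stated comparison, the obvious way to use the output is to see which predictors reach p < 0.05 in which arm. That is unreliable, because two small samples often fall on opposite sides of the threshold when the underlying effect is the same in both.

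The second problem is size. Splitting the sample by arm and then fitting five variables to a binary outcome leaves few events per coefficient, so odds ratios are exaggerated and the models appear to discriminate well when they do not. At stake is the credibility of the predictor findings, which section 3.1.1 makes a declared focus of the analysis.

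**Working it through.** **The plan's own figure.** No sample size or event count is given for the predictor models. The only size calculation is in section 2.7 for the main comparison: "we estimated an effect size of 0.6 (medium effect according to Cohen’s d", alpha 0.05 two-sided, power 0.8. A two-sample t-test calculation gives 44.59 per group against the stated 44.5, so it reproduces. It says nothing about the predictor models.

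**Number per arm.** The allocation ratio is not stated; 1:1 is assumed.

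- 60 / 2 = 30 per arm with no dropout
- 30 × 0.90 = 27 at 10% dropout
- 30 × 0.80 = 24 at 20% dropout

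**Events per variable (EPV).** EPV = (size of the smaller outcome class) / (number of predictors). The response rate is not given, so it is varied; 50% is the most favourable value possible.

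| Per arm | Response | Smaller class | EPV with 5 predictors |
|---|---|---|---|
| 24 | 50% | 12 | 2.4 |
| 30 | 50% | 15 | 3.0 |
| 24 | 30% | 7.2 | 1.4 |
| 30 | 30% | 9 | 1.8 |

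If medication or PANSS enters as more than one term, EPV is lower still. The larger targets elsewhere in the article do not remove the problem: 90 in total (Abstract) is 45 per arm and EPV at most 22.5 / 5 = 4.5; 60 per group (section 2.7) gives at most 30 / 5 = 6.0.

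**What this does to the estimates and to the arm comparison.** Simulation, 2000 trials per setting, five independent standard-normal predictors, one with the same true odds ratio (per SD) in both arms, about 50% responders. These settings are assumptions. The direct comparison is z = (b₁ − b₂) / √(se₁² + se₂²), judged at 1.96. Trials in which a fit failed to converge or ran to extreme values were set aside.

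| Per arm | True OR, both arms | Arms disagree on significance | Direct comparison significant | Median fitted OR | Trials set aside |
|---|---|---|---|---|---|
| 24 | 1.5 | 16% | 4.7% | 1.7 | 2.9% |
| 24 | 2 | 30% | 2.2% | 2.7 | 4% |
| 24 | 3 | 43% | 1.0% | 4.6 | 11.9% |
| 30 | 1.5 | 24% | 5.9% | 1.7 | 0.2% |
| 30 | 2 | 43% | 4.5% | 2.4 | 0.5% |
| 30 | 3 | 49% | 1.9% | 4.2 | 2.6% |

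Repeated runs across 24–30 per arm put disagreement at about 15–25% for OR 1.5, 29–43% for OR 2 and 41–52% for OR 2.7 (log OR 1), with the direct comparison wrong in about 2–6%. At a true log OR of 1.0 the mean fitted value was 1.5–1.7. With all five predictors pure noise, the mean apparent AUC was 0.73–0.78 against a true 0.50.

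**A ceiling on the disagreement rate.** If each arm has power p independently, the chance that exactly one is significant is 2p(1 − p), which cannot exceed 50%. At OR 2.7 and 27 per arm, p is about 0.43: 2 × 0.43 × 0.57 = 0.49. A simulated value slightly above 50% is simulation error.

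**Does pooling alone suffice?** A pooled logistic model on 48–60 participants with five main effects has EPV of at most 24 / 5 = 4.8 to 30 / 5 = 6.0, and less once treatment and interaction terms are added. Pooling supplies the missing contrast but does not cure the sparsity; a continuous outcome and fewer predictors per model are needed as well.

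**The case against.** The strongest reply is that section 3.1.1 never says that significance in one arm only will be read as treatment dependence. Two per-arm coefficients can be compared by a z-test. The phrase about predictors connected to treatment might mean predictors within each activity, or a separate analysis, and a condensed article may leave interaction terms and the responder definition to a fuller plan. This stands in part. A reader might infer that separate models can never show treatment dependence; that goes too far. What holds is that the article commits to the per-arm structure, names a treatment-connected aim and states no contrast that would serve it. The disagreement rates therefore apply only if the outputs are read in that way.

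It is also fair that disagreement near 50% is close to the worst case, which is why the whole range is given. The sparsity does not depend on how the outputs are read.

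Three stronger readings are not supported:

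- That PANSS would be predicting its own change through regression to the mean. The article does not say which PANSS score enters as a predictor, and its only reliability figures are interrater ones.
- That information is lost to a median split. No cut-point is given.
- That the predictors would decide who is offered music therapy. Nothing in the article says so.

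**Conclusion.** The point holds in this form: the planned models do not test whether a predictor's effect differs between arms, although treatment-connected predictors are an aim, and five variables per arm are too many for 24–30 people. EPV is at most 3.0 and is 1.4–1.8 at 30% response. Reading significance in one arm only as treatment dependence would mislead in roughly 15–52% of trials for odds ratios from 1.5 to 2.7, against about 2–6% for a direct comparison.

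The EPV ceiling rests on 1:1 allocation, the target of 60 and the plan's own dropout range. The error rates rest in addition on the simulated predictor distribution and effect sizes. A reader might infer that the trial's main result is in doubt; it is not. PANSS, BNSS and WHOQOL-BREF have their own mixed-model analysis, which this point does not touch. The change should be made, but the primary comparison does not depend on it.

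**What to change.** Replace the per-arm logistic models with one pooled linear or mixed model per outcome, on the continuous post-therapy score adjusted for its baseline, containing treatment, the predictor and their interaction. Enter one or a few prespecified predictors at a time. Report each interaction estimate with its 95% confidence interval, and label the analysis exploratory.

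Two outcomes need a sentence of their own. In Table 1 the alliance questionnaire is first completed after the fifth session, so it has no pre-treatment value to adjust for. As the table reads here, GAF is rated only at screening and baseline.

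For the outcomes already rated at baseline and post therapy, the cost is analysis wording only, with no new data. There are real downsides. Interactions will be imprecise at this size, which the intervals will show. Mutual adjustment among the five predictors is reduced. The question moves from response to mean score. Several interaction tests remain without multiplicity control: 5 predictors × 4 outcomes = 20, so about 20 × 0.05 = 1 false positive is expected if none is real.

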#### 3.1.2. Analysis of Compliance

A sensitivity analysis will compare compliance versus non-compliance. Compliance will be calculated based on the number of sessions received divided with number of sessions offered and multiplied by one hundred.

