## 2. Materials and Methods

### 2.1. A Randomized, Controlled and Blinded Study

The examination is a randomized, controlled, multi-site study, applying a blinded design including 25 sessions of manualized music therapy for the intervention group (group I) and 25 sessions of manualized music listening to selected playlists for the second arm with an active comparator (group II). The number of sessions is based on research concerning the dose response effect for music therapy for people with serious mental disturbances [28]. The arms of interventions are called intervention I and intervention II in the present study. Participants are rated at baseline, after 15 sessions and after 25 sessions post-therapy. At follow up (four weeks after post therapy at the end of study), a short, semi-structured interview will be performed with all participants. (See Table 1). Before baseline, all participants are informed (1) that they will be offered 25 sessions of music therapy, (2) that two different activities will be tested and compared (3) and that those performing the sessions are all referred to as therapists and are familiar with being together with people diagnosed with schizophrenia. (4) The participants will also be informed that recording of the musical activities might occur. All sessions will take place in the same equipped music therapy rooms. Intervention I is carried out by trained and experienced music therapists who are familiar with the population under examination, being carefully trained in and following a manual developed for this intervention in the study. Professional music therapists in Denmark all have a five-year full-time university BA/MA training, including several internship periods [29]. This training is based on a psychodynamic, humanistic and neuropsychological theoretical platform and is structured in three parallel running study tracks with equal weight through all five years. These tracks include an academic theoretical study track, a music-based improvisational methodological study track and a psychotherapeutic, self-experiential and clinical study track [29]. Due to the manual for Group I several music therapy methods and techniques can be applied including active methods (where the therapist and participant play or sing together, improvise, write songs or move to music), as well as receptive methods (where the therapist and participant listen to music together, either in the form of playlists selected by the music therapist, or in the form of participant-chosen or therapist-chosen music). The focus of the manual is about perspectives on the therapist’s way of being present and positions in the therapeutic relationship.

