#### 2.3.3. Treatment Schedule and Withdrawal Criteria

The treatment schedule is constructed to offer weekly sessions of 50 min of music therapy activities each 7 day +/− 1 day, resulting in a minimum of five days and a maximum of nine days between sessions. A session plan of 25 sessions is scheduled before the start of intervention and is accepted by the participant. If the participant fails to meet up to any of the scheduled sessions, with or without notice, the session will not be replaced. If the therapist cancels any of the scheduled sessions, replacements will be offered. The 25 scheduled sessions exclude holiday weeks. Participants will be withdrawn from the study as a whole if more than 30 days pass between two sessions or if the participant fails to turn up for more than five sessions. The participant will be reminded and warned by telephone if they fail to appear at three and four of the scheduled sessions, with a reminder of exclusion from further participation if a total of more than five lacking appearances occur. They will also be reminded if more than three weeks between scheduled sessions pass, often as part of a holiday, resulting in it being mandatory to attend the week after the holiday. Each therapist in the study is not allowed to plan for more than three combined weeks of holiday during each treatment schedule. Each time the participant fails to turn up without notice, the therapist will contact the participant to ensure the participant is safe and has planned not to attend this session. The participant will also be withdrawn from the study if they withdraw their informed consent. If hospitalization occurs during the study, the participant can continue in the study as long as the duration is short term (<5 days) and no change in medication has occurred.

Withdrawing from the study will in no way affect the individual participants’ treatment as usual.

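### The compliance sensitivity analysis compares groups defined by attendance after randomisation, largely completers against early leavers, so it cannot test the between-arm result; its denominator is also ambiguous

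*Protocol article*

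**What the plan says.** **Compliance analysis.** Protocol article, Section 3.1.2: "A sensitivity analysis will compare compliance versus non-compliance". Compliance is the "number of sessions received divided with number of sessions offered and multiplied by one hundred". No cut-off is given.

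**Schedule.** Section 2.3.3: "A session plan of 25 sessions is scheduled before the start of intervention and is accepted by the participant". Section 2.1 says participants are told "that they will be offered 25 sessions of music therapy". On absences, Section 2.3.3 states: "If the participant fails to meet up to any of the scheduled sessions, with or without notice, the session will not be replaced". Sessions cancelled by the therapist are replaced.

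**Withdrawal.** Section 2.3.3: "Participants will be withdrawn from the study as a whole if more than 30 days pass between two sessions". Repeated absence is a second ground for withdrawal, which applies "if the participant fails to turn up for more than five sessions". Withdrawing consent also ends participation.

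**Assessment of those who leave.** Section 3.1.1 provides a last assessment at discontinuation where it can be obtained, then says: "Participants will not be followed up on after this time point". Table 1 places the final visit within eight days of the last session.

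**Other analyses.** Section 3.1.1 also plans intention-to-treat and per-protocol analyses. The former uses all participants whatever their attendance.

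**The concern.** A sensitivity analysis should ask whether the main conclusion survives a change in its assumptions. Here the main conclusion is the difference between interventions I and II in the PANSS negative subscale. A comparison of attenders with non-attenders answers another question, and in groups that participants have sorted themselves into.

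The risk of confounding is plausible in this trial. Entry requires marked negative symptoms, and the qualifying items include emotional and social withdrawal (Section 2.3.1). Section 4.1.2 describes the population as having low motivation to take part. If such features affect both attendance and later PANSS scores, compliers may do better even if the sessions do nothing, and the result could be taken for a dose effect.

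Two further features add to the problem. The withdrawal rule ties low attendance to leaving early, so the two groups differ in when they are assessed. And the denominator of the index can be read in two ways that classify an early leaver in opposite directions.

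**Working it through.** The plan gives no compliance figure to reproduce. The steps below apply its own rules.

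**1. Range of the index in participants who are not withdrawn.** Inputs: 25 scheduled sessions; missed sessions not replaced; withdrawal when more than five are missed (all Section 2.3.3). Minimum = (25 − 5)/25 = 20/25 = 80%. So these participants score 80–100% on either reading of the denominator, and anyone below 80% has been withdrawn.

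**2. Index in participants withdrawn at the sixth miss.** If that miss falls at offered session k, attended = k − 6.

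| k | (k − 6)/k, running count | (k − 6)/25, fixed |
|---|---|---|
| 6 | 0% | 0% |
| 10 | 40% | 16% |
| 15 | 60% | 36% |
| 20 | 70% | 56% |
| 25 | 76% | 76% |

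Only a sixth miss at session 25 leaves a participant below 80% who has still gone through the whole schedule.

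**3. What a cut-off would compare.** At or near 80%, the contrast is largely completers, assessed after 25 sessions, against leavers, assessed earlier or not at all. Above 80%, completers who differ by at most five sessions are split, and those in the lower group are mixed with leavers. No cut-off makes it a test of I against II. On the expected drop-out of 10–20% (Section 2.7) and the current target of 60 (Section 5), the leavers would number about 0.10 × 60 = 6 to 0.20 × 60 = 12 over both arms.

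**4. The two denominators.** Table 1 times its visits by counting offered sessions as they occur, which suggests a running count. Sections 2.1 and 2.3.3 suggest 25.

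| Participant | Running count | Fixed at 25 |
|---|---|---|
| Attends 4 of 4, then withdraws consent | 4/4 = 100% | 4/25 = 16% |
| Attends 4, sixth miss at session 10 | 4/10 = 40% | 4/25 = 16% |
| Attends 10, misses 4 in a row, withdrawn for the gap | 10/14 = 71% | 10/25 = 40% |

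The first two received the same number of sessions. They get equal scores only with the fixed denominator.

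**5. Self-selection, illustration only.** A simulation gave sessions no effect on outcome. Each person had a standard normal prognosis u, and the chance of attending a session was Φ(Φ⁻¹(0.85) + 0.7u). Compliers were those missing at most five of 25. All of these are assumptions, not figures from the plan.

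| Correlation of prognosis with outcome | Spurious complier difference (SD) |
|---|---|
| 0 | about 0 |
| 0.2 | 0.30 |
| 0.3 | 0.46 |
| 0.5 | 0.76 |

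The trial is planned on an effect of 0.6 (Section 2.7), so a moderate correlation could produce a difference of that order. About 64% completed in the simulation, fewer than the 80–90% implied by the plan's drop-out figure. The table shows the mechanism, not the size to expect.

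**The case against.** **The section is brief and details may sit elsewhere.** The cut-off and any adjustment may be in an analysis plan that is not shown, and their absence is not counted here. The sentence might also mean comparing the treatment effect between compliance strata. That would keep the arms, but the strata would still be formed after randomisation, and compliers in one arm need not resemble compliers in the other. Near an 80% cut, the lower stratum would also be very small.

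**A reader might infer that low attenders have no outcome data.** The documents do not support this. Section 3.1.1 provides an assessment at discontinuation where possible, those who leave after the session-15 visit have that visit too, and a sixth miss at session 25 can be assessed on time. The planned mixed model can use such data. What stands is that nearly all low attenders lack an assessment at the planned end of 25 sessions.

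**A reader might infer that the index scores early leavers as fully compliant.** That follows only from the running count. The text on 25 sessions offered and scheduled in advance supports the other reading. What stands is the ambiguity.

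**A reader might infer that compliers are bound to look better.** The documents do not say that negative symptoms drive attendance, and with no correlation the simulation shows no difference. What stands is that the contrast is open to this bias and cannot separate it from an effect of sessions.

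**The analysis is supplementary.** This stands, and it limits the weight of the point.

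**Conclusion.** The point holds for a supplementary analysis. The comparison in Section 3.1.2 is defined by a post-randomisation variable, so it is not a sensitivity analysis of the randomised result at any cut-off. Under the plan's own withdrawal rule, participants who stay score 80–100% and everyone below 80% has been withdrawn, so compliance is largely confounded with completion and with the time of assessment. The denominator supports two readings, which give the same early leaver 100% or 16%.

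The 80% bound and the index values follow directly from the stated rules. The count of 6–12 leavers assumes the plan's expected drop-out and its current target of 60. The size of any bias is not known from the documents. The intention-to-treat analysis in Section 3.1.1 is unaffected. The change is worth making because it is cheap and prevents a confounded contrast from being read as support for the main result.

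**What to change.** 1. Define the denominator in Section 3.1.2 as the 25 scheduled sessions for every participant. Replacement of therapist-cancelled sessions already makes 25 attainable.
2. Report compliance by arm descriptively. Label any comparison of compliers with non-compliers as descriptive, not as a sensitivity analysis or as evidence of a dose effect.
3. Run the sensitivity analysis on the randomised contrast in all randomised participants. One option is delta-adjusted multiple imputation for those who stopped, with delta varied by arm until the conclusion changes.
4. In any per-protocol analysis, keep the randomised arms, apply the same attendance cut in both, adjust for the baseline PANSS negative score and label the result supportive.

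The cost is a change of wording and modest extra analysis of data already being collected. Step 3 adds an untestable assumption about delta, which the range of values makes visible. The withdrawal rule itself need not change.
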